The Mindfulness-Based Stress Reduction (MBSR) program was created by Jon Kabat-Zinn and colleagues at the University of Massachusetts Medical Center in 1979, and it is an intervention whose effects on mental health and quality of life have produced several studies worldwide, both in clinical and non-clinical populations. Several protocols have been developed based on the MBSR aimed at specific populations, such as the Mindfulness-Based Health Promotion (MBHP) program developed by the Mente Aberta Brazilian Center for Mindfulness and Health Promotion. The MBHP program was inspired by the original MBSR model but adapted to the context of the Brazilian health care (SUS) system, addressing chronic conditions and mental disorders as well [36,37,38].

Positive psychology seeks to understand positive emotions, psychological potentialities and healthy human/social/institutional functioning, and apply this knowledge to help people and institutions, with a focus on the prevention and promotion of mental health [39]. At first, positive psychology focused a lot on happiness and subjective well-being [40,41]. In a second step, the studies gained a broader view of psychological well-being and another similar proposal entitled PERMA, which is composed of the following five spheres: *positive emotions*—*P; engagement*—*E; relationships*—*R; meaning*—*M; achievement*—*A* [42,43]. Although positive psychology aims to be a way of looking at life, some psychotherapeutic proposals, such as positive psychotherapy (PPT), have been developed, and clinical studies have been replicated in different clinical and cultural contexts [44,45].

The proposed study is a randomized control trial comparing TBCT, MBHP and PPT to treat patients with PTSD due to traumatic exposure during the COVID-19 pandemic. Our hypotheses are that TBCT is at least as effective as MBHP and possibly more effective than PPT, considering that no studies were found assessing its efficacy in patients with PTSD.

Our primary objectives are to assess the efficacy of TBCT for patients with PTSD because of or during the COVID-19 pandemic and to compare its efficacy with that of MBHP and PPT, with all therapies delivered online in the same sample. Secondarily, we aim to quantitatively assess symptoms of depression, anxiety and guilt, as well as well-being and the strength of the therapeutic alliance.

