### 2.2. Hypotheses

According to the literature and the results of other clinical trials, we have elaborated the following hypotheses:

**Hypotheses 1** **(H1)**.*TBCT and MBHP in online modalities are statistically different from PPT online in reducing the symptoms of PTSD*;

**Hypotheses 2** **(H2)**.
*TBCT and MBHP in online modalities are of greater effect size in reducing PTSD symptoms compared to the control (PPT);*

**Hypotheses 3** **(H3)**.*TBCT and MBHP in online modalities contain the largest effect sizes in reducing the symptoms of guilt over the traumatic event compared to the control*;

**Hypotheses 4** **(H4)**.*TBCT and MBHP in online modalities are statistically different from the control, with a larger effect size, in improving quality of life (or disability)*.

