### 2.10. Sample Size

The sample size calculation was estimated using the G*Power software version 3.1 [76], considering a mixed design. Parameters that were taken into account were the F test and repeated measures ANOVA for comparison between groups, for an effect size of 0.25, α criterion of 0.05 and power of (1−β) 0.80, three groups design (TBCT X MBHP X WBT), three measures (baseline, mid-treatment and final assessment), and an a priori correlation between the repeated measures of 0.50. Hence, a sample of 108 participants was obtained, with a numerator of 2 and a denominator of 105 degrees of freedom, for a critical F of 3.08. Considering a 25% dropout rate, a total of 135 participants was estimated.

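### The 80% power in section 2.10 belongs to the three-arm omnibus F test, which does not establish H1; on the same inputs, power to show that TBCT and MBHP each differ from PPT is about 66% at 108 patients

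*Protocol article*

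**What the plan says.** Section 2.10 (Sample Size) names the powered test as "the F test and repeated measures ANOVA for comparison between groups". Its inputs are "for an effect size of 0.25", "α criterion of 0.05", "power of (1−β) 0.80", three groups, three measures (baseline, mid-treatment, final) and a correlation of 0.50 between measures. The result is given as: "Hence, a sample of 108 participants was obtained, with a numerator of 2 and a denominator of 105 degrees of freedom, for a critical F" (the value given is 3.08). The total is then raised to 135 for dropout.

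Section 2.2 (Hypotheses) gives H1 as: "TBCT and MBHP in online modalities are statistically different from PPT online in reducing the symptoms of PTSD". H2 treats PPT as the control.

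The Introduction sets the primary objective as assessing TBCT and "to compare its efficacy with that of MBHP and PPT, with all therapies delivered online in the same sample".

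Section 2.15 (Statistical Methods) plans generalized estimating equations (GEE) for change over time and between groups at 0.05, and names no contrast between arms.

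**The concern.** The only stated power is for a global test, while the first hypothesis concerns two specific comparisons with one reference arm. A significant 2-df test can come from one therapy alone, or from a difference between TBCT and MBHP, so the trial can reach the result it was sized for without supporting H1. A reader who takes 80% as the chance of confirming H1 would be too optimistic. A reader who takes a significant F as confirmation would credit MBHP or TBCT with a difference from PPT that was not shown.

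**Working it through.** **Inputs.** From section 2.10: f = 0.25, alpha 0.05, m = 3 measures, correlation rho = 0.5, N = 108. From section 2.13: 1:1:1 allocation, so 36 per arm. Assumed here: two-sided 0.05 for each contrast, no multiplicity adjustment, error variance pooled over the three arms (105 df).

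**Step 1: reproduce the stated figure.** Noncentrality = f² × N × m / (1 + (m − 1) × rho) = 0.0625 × 108 × 3 / 2 = 10.125. With 2 and 105 df the critical F is 3.083 and power is 0.809. At N = 105 power is 0.797, so 108 is the smallest balanced total above 0.80. The stated N, degrees of freedom and critical F all reproduce, as the omnibus between-groups test.

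**Step 2: turn f into arm differences.** If TBCT and MBHP are equally better than PPT by d, the standard deviation of the three means is d × √2 / 3. So d = 0.25 × 3 / √2 = 0.530 SD.

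**Step 3: one contrast with PPT.** The SD of a patient's three-measure average is √((1 + 2 × 0.5) / 3) = 0.816. The standardised difference is 0.530 / 0.816 = 0.650, and the noncentrality of the t test is 0.650 × √(36 / 2) = 2.756. Power is about 78% for each contrast.

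**Step 4: both contrasts.** They share the PPT arm and the pooled variance, so joint power was simulated (2,000,000 draws): 66.1%. The F test is significant without both contrasts being significant in about 15.5% of such trials.

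**Step 5: other patterns at the same f, 36 per arm.** The ratio is the smaller difference from PPT divided by the larger.

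| Ratio of the two effects | Omnibus F | Smaller effect vs PPT | Larger effect vs PPT | Both |
|---|---|---|---|---|
| 1.0 | 81% | 78% | 78% | 66% |
| 0.9 | 81% | 73% | 82% | 65% |
| 0.8 | 81% | 66% | 85% | 61% |
| 0.5 | 81% | 35% | 88% | 34% |
| 0 (one therapy equals PPT) | 81% | 5% | 78% | 3% |

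In the 0.5 row, d = 0.25 × √6 = 0.612 for the larger effect and 0.306 for the smaller. In the last row H1 is false, yet the powered test still rejects in 81% of trials. The omnibus power does not respond to the feature that decides H1.

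**Step 6: a pooled contrast.** Testing the average of TBCT and MBHP against PPT has 88% power when the effects are equal. With MBHP midway it still has 78%, although MBHP against PPT has only 35%.

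**Step 7: what the 66% is not.** It is the power for an average over three visits that include baseline, with the full difference present at each. Section 2.15 compares changes. As an illustration, suppose 0.530 SD is the difference at the final visit only (an assumption):
- Change from baseline has SD √(2 × (1 − 0.5)) = 1, so the noncentrality is 0.530 × √18 = 2.25 and joint power about 45%.
- Baseline adjustment has SD √(1 − 0.5²) = 0.866, so the noncentrality is 2.60 and joint power about 60%.

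**The case against.** **Nothing in section 2.10 is miscalculated.** This stands. The section names its test and prints its 2 numerator degrees of freedom, and sizing a three-arm trial on the omnibus test is common. A reader might infer that 108 is an arithmetic error, or that the article promises 80% for H1. Neither is supported. The fault is that the only power given belongs to a test that does not answer the first hypothesis.

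**H1 states no rule that both contrasts must succeed.** This stands in part. Read as two separate claims, each has 78%, close to 80%. Read as one pooled contrast, it has 88%. A reader might therefore take 66% as a ceiling under any reading, which it is not: it is the maximum only when both contrasts are required and f is held at 0.25. Requiring both is still the plain sense of H1. The article states no pooled contrast, and a pooled contrast would not show that each therapy differs from PPT.

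**H1 is not a settled target.** This stands. The Abstract expects no statistical difference among the three arms. The Introduction has TBCT at least as effective as MBHP and possibly better than PPT. Neither matches H1. This adds to the problem, because the 80% does not attach to any of those statements either: a non-significant F would not demonstrate that the arms are alike.

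**Contrasts and success rules can sit in an analysis plan.** This is fair, and the absence of that detail from section 2.15 is not the point. The mismatch lies between two things the article does state: the powered test and the hypothesis.

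**Conclusion.** The point holds as a mismatch between test and hypothesis. Under the sample-size model, with equal effects of TBCT and MBHP against PPT and each contrast at two-sided 0.05, power for H1 is about 66% at 108 evaluable patients, against 80.9% for the omnibus test. It falls as the two effects diverge at the same f, to 34% with MBHP midway. A multiplicity adjustment would lower it further: Bonferroni at 0.025 each gives 54%.

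The figure rests on f = 0.25 as given, on reading H1 as two differences from PPT, and on 108 evaluable patients. It should not be read as the power of the planned GEE comparison of change, for which the article does not give enough to fix a number.

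**What to change.** **Section 2.10.** State that 80% applies to the omnibus three-arm test only. Add that, under the same model, power for H1 is about 66% at 108 evaluable patients (about 78% for each contrast). List the assumptions: f = 0.25, correlation 0.5, three-measure average, two-sided 0.05, TBCT and MBHP equally better than PPT. Note that this is not the power of a GEE change-from-baseline contrast, and recompute it for the model in section 2.15.

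**Section 2.15.** State that H1 is judged from two contrasts, TBCT against PPT and MBHP against PPT, and is claimed only if both are significant at 0.05. A significant overall group test alone does not count as support for H1.

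**Abstract, Introduction and section 2.2.** Reconcile the three statements so that one primary hypothesis stands. If it is not H1, the contrasts and the power statement should follow the one chosen.

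**Cost.** Wording, two contrasts from the model already planned, and one recomputation. No extra patients are needed to make the statement correct; the sponsor would be accepting a less favourable stated power. For scale, 80% joint power under the sample-size model would take 141 to 144 evaluable patients (80.0% and 81.1%).

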## Abstract

Background: Research suggests the use of different forms of therapy as a way of decreasing dropout rates in the treatment of post-traumatic stress disorder (PTSD). The psychotherapies to be assessed in this study are trial-based cognitive therapy (TBCT), mindfulness-based health promotion (MBHP) and positive psychotherapy (PPT). Objectives: (1) to assess the online efficacy of TBCT compared to MBHP and PPT to reduce the symptoms of PTSD in the context of the Coronavirus Disease 2019 (COVID-19) pandemic; (2) to compare the efficacy of these psychotherapies in improving anxiety, depression, guilt and in promoting well-being; and (3) to describe how professionals perceive online treatment. Methods: A randomized, multicenter, single-blind clinical trial will be conducted, with three separate arms. An estimated sample of 135 patients will receive either TBCT, MBHP or PPT and will be treated through online, individual, weekly visits, totaling 14 sessions. The primary outcome will be CAPS-5 and secondary outcomes will be HADS and WHO-5. The variables used to mediate these outcomes will be the Trauma-Related Guilt Inventory (TRGI), Negative Core Beliefs Inventory (NCBI) and the California Psychotherapy Alliance Scale (CALPAS-P). Expected results: PTSD symptoms are expected to be reduced after TBCT, MBHP and PPT. No statistical difference is expected to be found among the three. Discussion: The present study will evaluate and contribute towards the development of new psychotherapeutic options for patients with PTSD. The results of this study will allow the dissemination of new effective and adaptable interventions for patients with PTSD.

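### The allowance for 25% dropout is short: 135 randomised leave about 101 completers, not the 108 that the power calculation needs

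*Protocol article*

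**What the plan says.** Section 2.10 of the protocol bases the sample size on "the F test and repeated measures ANOVA for comparison between groups", "for an effect size of 0.25", with "α criterion of 0.05 and power of (1−β) 0.80". There are three groups, three measurement occasions (baseline, mid-treatment and final) and an assumed correlation of 0.50 between measures. The result is given as "Hence, a sample of 108 participants was obtained", with 2 and 105 degrees of freedom and a critical F of 3.08. The dropout step follows in one sentence, without a formula: "Considering a 25% dropout rate, a total of 135 participants was estimated".

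The Abstract repeats the total: "An estimated sample of 135 patients will receive either TBCT, MBHP or PPT". So 135 is the number treated, not a screening figure or a count of completers. Section 2.13 (Randomization and Concealment) fixes equal allocation, 1:1:1.

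**The concern.** The total of 135 is 108 increased by a quarter of 108. A 25% dropout rate takes a quarter of those who enter, and a quarter of 135 is more than a quarter of 108. The allowance therefore cannot leave 108 patients at the rate it names.

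At stake is whether the trial, run exactly as planned and with exactly the dropout it expects, has the power it states. The figure also sits in the Abstract, and the Introduction gives high dropout in PTSD treatment as a main reason for the study, so the allowance deserves to be right.

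**Working it through.** **Inputs** (all from section 2.10, except allocation from section 2.13): Cohen's f = 0.25; α = 0.05; k = 3 groups; m = 3 measures; correlation ρ = 0.50; target power 0.80; base N = 108; dropout d = 0.25; total 135; allocation 1:1:1.

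**Step 1: reproduce the base figure.** For the between-groups test in a repeated measures ANOVA, as G*Power computes it:

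- noncentrality λ = f² × N × m / (1 + (m − 1)ρ) = 0.0625 × N × 3 / 2 = 0.09375 N
- degrees of freedom k − 1 = 2 and N − k
- power = probability that a noncentral F with noncentrality λ exceeds the critical F

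At N = 108: λ = 10.125, degrees of freedom 2 and 105, critical F 3.083, power 0.809. The protocol's N, degrees of freedom and critical F all reproduce, so the base calculation is not in question.

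**Step 2: the dropout step.**

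- Required total: 108 / (1 − 0.25) = 144, or 48 per arm.
- Stated total: 135 = 108 × 1.25.
- Completers from 135 at 25% dropout: 135 × 0.75 = 101.25, about 101.
- Dropout at which 135 does leave 108: 1 − 108/135 = 27/135 = 20%.
- Shortfall: 144 − 135 = 9 randomised patients, and 9/135 = 6.7%.

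**Step 3: power by number of completers, same inputs.**

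| Completers | λ | Power |
|---|---|---|
| 99 (33 per arm) | 9.281 | 0.770 |
| 101 | 9.469 | 0.779 |
| 105 (35 per arm) | 9.844 | 0.797 |
| 106 | 9.938 | 0.801 |
| 108 (36 per arm) | 10.125 | 0.809 |

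The smallest N that reaches 0.80 is 106, and the smallest with equal arms is 108. The 101 completers expected at 25% dropout fall below both.

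**The case against.** Nothing elsewhere in the protocol corrects the figure, so the case on the other side concerns its weight.

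- **The planned analysis keeps everyone.** Section 2.15 (Statistical Methods) plans intention to treat with multiple imputation and generalised estimating equations. Patients who drop out have baseline data, and some will have the mid-treatment assessment. The 0.779 treats each of them as contributing nothing, so the real loss may be less than 2 points. This stands as a limit on the size. It does not rescue the sentence: imputation cannot restore the information of complete cases, and a calculation that inflates for dropout is by its own logic counting completers.
- **The loss is small beside the other assumptions.** If the correlation were 0.45 rather than 0.50, 101 completers would give power 0.801; at 0.55 even 108 would give only 0.788. At 101 completers the effect detectable with 80% power moves from the planned f of 0.25 to about 0.256. This stands too. It shows that the design is not endangered, but the stated figures still disagree.
- **The 25% may have been meant as an increase over 108.** No formula is given, so multiplication by 1.25 is inferred from the match. The text calls the 25% a dropout rate, however. Read as an increase, it would cover 20% dropout, and the sentence would still need changing.

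The Introduction also cites 31% dropout in trials with military service members. At that rate about 93 of 135 would complete and power would be 0.742. The protocol does not adopt that rate and the population differs, so the conclusion here does not rest on it.

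**Conclusion.** The concern holds. Section 2.10 cannot deliver 25% dropout, 80% power and 135 participants together. On its own inputs, 135 covers 20% dropout; at 25% about 101 patients complete and power is 0.779, which is 2.1 points below the target and 2.9 points (0.809 − 0.779, unrounded) below the power at 108.

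The power figures assume the protocol's own test, effect size and correlation, and count completers only. The arithmetic of the dropout step needs none of those assumptions. The error is certain but its effect is modest: it biases no comparison and does not undermine the design. It should be corrected because it is a wrong statement about the headline sample size.

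**What to change.** Keep 135 and rewrite the last sentence of section 2.10 to say that 135 randomised patients retain 108 completers at 20% dropout (power 0.81), and that at 25% dropout about 101 complete, with completers-only power of about 0.78. If the sponsor is relying on partial data from dropouts to recover power, the same sentence should say so. This costs one sentence and a slightly less favourable stated power. It needs no extra patients and leaves the Abstract unchanged.

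If the sponsor prefers to keep 25% dropout with 80% power, the total must become 144 (48 per arm). That means 9 more patients, and the total in the Abstract must change to match.

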### 2.11. Randomization and Sequence Generation

After screening and initial evaluation, the study coordinator will refer the patient to the person responsible for randomization, who does not participate in the patient treatment. The randomization process, at www.random.org (accessed on 1 December 2021), will be done through a computer-generated table of random numbers, allocating patients to a particular group. After that, the patient will be referred to the psychotherapist.

Six evaluators, blinded to the intervention group, will be responsible for assessing and referring the eligible patient to the study coordinator, who will proceed with the randomization. Each evaluator will assess the same patients throughout the study.

### 2.12. Implementation

After the patient has signed the informed consent and has been evaluated for inclusion criteria and baseline measurements, the assessor will contact the research coordinators informing them about the new patient and providing their patient number. Based on the random list, the coordinators will then contact the therapist to inform him/her about the new patient now available for treatment.

### 2.13. Randomization and Concealment

Patients who meet all eligibility criteria and complete the baseline assessments will be randomly allocated (1:1:1) to TBCT, MBHP or PPT. Randomization is based on a true random number service (http://www.random.org, accessed on 01 December 2021) and will be conducted by a member of the research team who is blinded to patient characteristics and is not involved in any other aspects of the study. The study therapists will be blinded to assessment outcomes, and the research assistant conducting post- and follow-up assessments will be blinded to participant condition.

### 2.14. Interventions Similarities and Differences

The interventions have similarities and differences. First of all, TBCT aims to identify thoughts, emotions and behaviors on three levels of cognition, with the purpose of changing them especially at the third level, where it is meant to identify and modify CBs, which mediate the change of thoughts and behaviors characterized as symptoms. On the other hand, MBHP and PPT are not meant to identify distorted cognitions, unpleasant emotions and dysfunctional behaviors or change them directly. MBHP, for instance, teaches from the very first sessions how to pay attention to the present moment and how to use various mindfulness practices. It teaches the patient how to identify rewarding characteristics and valuable personal attributes, without correlating these to pathological thoughts, emotions or behaviors. On the other hand, the focus of PPT is to enhance personal strengths; behaviors related to gratitude, kindness and appreciation; and thoughts related to well-being. Therefore, each intervention advocates a different change process: TBCT modifies CBs, MBHP teaches meditation skills and PPT guides the patient into enhancing personal strengths and virtues.

### 2.15. Statistical Methods

The collected data will be analyzed statistically using the Statistics Package for Social Science software (SPSS), version 24.0 [77]. Clinical and demographic categorical variables will be analyzed with *X*^2^ (sex, education, color or race, and dropout rate) and continuous variables will be assessed with one-way ANOVA (age and scale scores). Missing data for both primary and secondary outcome measures will be analyzed by intention to treat (ITT) and multiple imputation (IM), with five imputed databases taking baseline and sociodemographic data and assuming the random chance mechanism. Generalized estimation equations (GHG), taking time as a covariate, will be performed to compare changes in scores over time and between groups (TCP, MBSR and PP). Effect sizes will be evaluated according to Cohen’s tests. The assumed level of statistical significance will be 0.05.

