### 2.8. Outcomes

Primary outcomes will be assessed by the reduction in PTSD symptoms, measured through CAPS-5. Secondary outcomes will be the improvement in symptoms of anxiety, depression and well-being. Mediator variables will also be assessed, measuring negative CBs, guilt and the strength of the therapeutic alliance. All scales will be applied by a blind assessor to the intervention groups before randomization (Initial Assessment), after seven sessions (Intermediate Assessment) and after 14 sessions (Final Assessment). They will also be applied in the 3-, 6- and 12-month follow-ups. Table 1 shows the flow of sessions and evaluations over the study period. Table 1 shows the SPIRIT diagram.

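### The missing-data rule in 2.15, read with the protocol's own outcome labels, does not reach guilt (TRGI), the endpoint of H3, and its imputation model names no session-7 scores

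*Protocol article*

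**What the plan says.** **The rule.** Protocol article, 2.15: "Missing data for both primary and secondary outcome measures will be analyzed by intention to treat (ITT) and multiple imputation (IM"). The same sentence goes on to describe how the imputation is built: "with five imputed databases taking baseline and sociodemographic data and assuming the random chance mechanism". The analysis is GEE, which "will be performed to compare changes in scores over time and between groups". No scale is named in that sentence.

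**The labels.** Section 2.8 defines the secondary group: "Secondary outcomes will be the improvement in symptoms of anxiety, depression and well-being". It then sets guilt apart in a further group: "Mediator variables will also be assessed, measuring negative CBs, guilt and the strength of the therapeutic alliance". Section 2.9 uses the same three groups: CAPS-5 is primary, HADS and WHO-5 are secondary, and TRGI, NCBI and CALPAS-P are mediators. The outcome list in the Abstract agrees.

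**The aims.** H3 in 2.2 predicts that TBCT and MBHP "contain the largest effect sizes in reducing the symptoms of guilt over the traumatic event" relative to the control. Objective 2 in the Abstract is "to compare the efficacy of these psychotherapies in improving anxiety, depression, guilt and in promoting well-being". The Introduction says: "Secondarily, we aim to quantitatively assess symptoms of depression, anxiety and guilt, as well as well-being and the strength of the therapeutic alliance".

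**The concern.** Guilt has two roles. The outcome sections treat it only as a mediator. The hypotheses and objectives treat it as something on which the arms are compared, beside anxiety and depression. The missing-data rule is written in terms of the outcome labels, so an analyst who follows 2.8, 2.9 and 2.15 together could impute HADS and not TRGI, although objective 2 treats both as efficacy targets.

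TRGI would then go into GEE on whatever observations exist. Unweighted GEE on incomplete data generally needs dropout to be unrelated to earlier scores. If patients with more guilt at session 7 are likelier to leave, and this differs between arms, the arm that loses more of them looks better on guilt at session 14 for reasons unrelated to therapy.

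Such a difference between arms is conceivable here. The sample size in 2.10 allows for 25% dropout, 2.15 lists dropout rate among the variables to be tested, and 2.7 cites an earlier trial in which dropout was lower with TBCT than with prolonged exposure.

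**Working it through.** The plan gives no figure on this point to reproduce, so the check has a reading step and an illustration.

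**1. Does the rule reach TRGI?**

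| Place in the protocol article | Status of guilt |
|---|---|
| Abstract, objective 2 | efficacy comparison |
| Introduction, last paragraph | secondary aim |
| 2.2, H3 | between-arm hypothesis |
| Abstract outcome list, 2.8, 2.9 | mediator |
| 2.15 | not named; rule covers primary and secondary outcome measures |

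The terms used in 2.15 are defined in 2.8 and 2.9. On those definitions TRGI lies outside the rule. On the Introduction's wording it could lie inside.

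**2. What would follow if TRGI were not imputed?**

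Assumptions (none is in the protocol unless noted):
- Standardised guilt scores correlate 0.5 (baseline with session 7), 0.4 (baseline with session 14) and 0.6 (session 7 with session 14).
- There is no true arm difference.
- Dropout occurs after session 7, and its log-odds rise by 1 per SD of session-7 guilt.
- GEE uses an independence working correlation, so the session-14 contrast equals the difference in observed means.
- Dropout by arm varies around the protocol's 25%.

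Let m be the mean session-7 score, in SD units, of patients who stay. Numerical integration of the logistic model gives m = −0.133, −0.173, −0.213, −0.253 and −0.292 at 15%, 20%, 25%, 30% and 35% dropout. If dropout is unrelated to the score, m = 0.

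*No imputation.* The expected session-14 mean of stayers is 0.6 × m.
- 15% v 35%: 0.6 × (0.292 − 0.133) = 0.096 SD
- 20% v 30%: 0.6 × (0.253 − 0.173) = 0.048 SD
- 25% in both arms, score-related in one only: 0.6 × 0.213 = 0.128 SD
- 25% in both arms, same mechanism: 0

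*Imputation within arm from baseline only.* Let b be the slope of session 14 on baseline among stayers. Dropouts differ from stayers at baseline by −0.5 × m / (dropout share). Filling in that share shifts the arm mean by −b × 0.5 × m. The arm's bias becomes m × (0.6 − 0.5b). Selection lowers b slightly from 0.40, to 0.37–0.38, so the multiplier is 0.41–0.42.
- 15% v 35%: 0.292 × 0.416 − 0.133 × 0.410 = 0.067 SD
- 20% v 30%: 0.253 × 0.415 − 0.173 × 0.411 = 0.034 SD
- 25%, one arm only: 0.213 × 0.413 = 0.088 SD

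The remaining share is 0.067/0.096 = 0.70, 0.034/0.048 = 0.70 and 0.088/0.128 = 0.69. About 30% of the bias is removed.

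*Imputation within arm from baseline and session 7.* Dropout depends only on session 7, which is now in the model, so the expected bias is 0. Simulation with 2,000,000 patients per arm gave differences within 0.002 SD of zero in every scenario.

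**3. Scale.** The planning effect in 2.10 is f = 0.25. If two arms are equal and differ from PPT by d, then f = d × √2/3, so d = 0.25/0.471 = 0.53 SD. Borrowing that figure for guilt, the un-imputed bias is 0.048/0.53 = 9% to 0.128/0.53 = 24% of it.

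**The case against.** **The protocol never says that guilt is analysed on available cases only.** A reader might infer this from 2.15, but the text does not support it. The sentence does not say only, excludes no scale and mentions no complete-case analysis. Un-imputed GEE is the default consequence of the labels, not a stated plan. The Introduction's secondary aims include guilt, and on that reading the rule covers TRGI. This stands, and it limits the point to a rule whose wording does not clearly reach the H3 endpoint.

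**Missing-data handling for mediators usually belongs in the analysis plan, which is not shown.** This is fair for mediators as such. Here, however, the article itself fixed a scope, and that scope does not fit its own H3.

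**The main source of the bias is the predictor set, not the list of scales.** This is correct: baseline-only imputation leaves about 70% of it. CAPS-5 would be exposed in the same way if its dropout depended on session-7 scores, so one should not infer that CAPS-5 is protected and guilt is not. Section 2.15 does not say that session-7 scores are barred from the model, but it does not name them either.

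**Two further inferences are not supported.**
- The same complaint does not carry over in full to core beliefs, because no hypothesis in 2.2 compares NCBI between arms.
- Mediation results cannot be shown to be attenuated. The protocol states no mediation model, and Table 1 measures TRGI, NCBI and CAPS-5 at the same visits, so a patient who misses session 14 would generally lack all three.

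**Conclusion.** The point holds in a limited form. On the labels in 2.8 and 2.9, the ITT and imputation rule in 2.15 does not cover the endpoint of H3; on the Introduction's wording it might. The imputation described would also deal poorly with dropout that follows session-7 scores, for any scale.

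The possible size is modest: in the three scenarios with unequal dropout, 0.05 to 0.13 SD un-imputed, about 0.03 to 0.09 SD with baseline-only imputation, and about 0 with session 7 included. All of this rests on assumed correlations, an assumed dropout slope and dropout that differs between arms in rate or mechanism. With one mechanism common to both arms the bias is 0. A working correlation other than independence would change the un-imputed figures.

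This is a cheap improvement to make before results are seen. It does not show that the H3 analysis is wrong.

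**What to change.** In 2.15, replace the reference to primary and secondary outcome measures with the scales by name: CAPS-5, HADS, WHO-5 and TRGI, plus NCBI if it is to be analysed. The rule then no longer depends on whether guilt is called a mediator or a secondary outcome.

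In the same sentence, state that these scales are imputed jointly by arm in one model that includes the observed session-7 scores as well as baseline and sociodemographic data. Both changes are needed, since naming the scales alone removes only about 30% of the illustrative bias.

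The cost is one or two sentences and no new data. The downside is a larger imputation model to check for convergence, with 135/3 = 45 patients planned per arm.
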